### Statistical analyses

*Model building.* Intent-to-treat (ITT) analyses of condition effects will be evaluated using mixed effects growth models fit with SAS 9.2 PROC MIXED [50]. Individual variability in outcomes from posttest to 2-year follow-up was modeled adjusting for pretest outcome values. Following Singer and Willet [51], when constructing the longitudinal models we will (a) examine empirical growth plots; (b) fit an unconditional means model; (c) fit an unconditional linear growth model; (d) fit unconditional non-linear models; and (e) compare models of longitudinal change using the Akaike Information Criterion. Condition, time (coded in months since posttest), and a condition × time interaction will be added to the unconditional model. We will estimate a growth model for each continuous outcome. We will report the results of planned contrasts from these models, contrasting each pair of conditions, reporting condition differences in the model implied least-square means derived from the time and condition × time interactions at 1- and 2-year follow-up. We will report effect sizes that are equivalent to Cohen’s *d* [52]. We will use full information maximum likelihood (ML) estimation to impute missing data because this intent-to-treat approach produces more accurate and efficient parameter estimates than alternative analytic approaches such as analyzing only participants who provide complete data, making multiple imputation the recommended procedure for handling missing data [53]. Missing data will be imputed using PROC MI using baseline levels of the outcomes, condition, and demographic factors (age, race, and parent education). Based on the recommendations [53], we will impute 50 data sets. Model parameters and standard errors were combined following Rubin [54] and implemented using PROC MIANALYZE. Cox proportional hazard models, fit with STATA [55] will test whether eating disorder onset over 2-year follow-up was significantly lower in each condition versus each other condition. Schoenfeld residuals will be examined to test the proportional hazards assumption. Hazard ratios and number needed to treat (NNT; [56]) are provided as measures of effect size. Because hazard models accommodate right censoring, we will not impute missing incidence data. Given that 88% of the effects from previous *Body Project* trials have replicated in 22 controlled trials from independent teams [15], we will use a p-value of 0.05 for all inferential tests because this usually balances risk for type I and type II errors.

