## The intervention

The *Body Project* is a group-based ED prevention program based on the principles of cognitive dissonance. According to Festinger [27], cognitive dissonance occurs when there is an inconsistency between one’s beliefs and one’s actions. This inconsistency creates psychological discomfort, which motivates the individual to reduce cognitive discord by changing their beliefs to align with their actions. In the *Body Project*, participants collectively critique the thin beauty ideal through a series of verbal, written, and behavioral exercises. Engaging in these activities prompts participants to align their attitudes with their publicly displayed behaviors, which results in a reduction in pursuit of the thin beauty ideal, which in turn is theorized to reduce body dissatisfaction and ED symptoms. Consistent with this theory, reductions in pursuit of the thin beauty ideal mediated the effects of the *Body Project* on ED symptom reduction [28]. During the four sessions, the participants define the appearance ideal, discuss costs of pursuing this ideal, attempt to dissuade group facilitators from pursuing the appearance ideal in role-plays, and engage in discussions about the negative effects of social comparison [29] and social media. Written home exercises are conducted between sessions and debriefed with the group in the following meeting. We have previously translated the latest version of the *Body Project* script [15] to Norwegian for the first time and piloted a diabetes-specific version among Norwegian young women with type 1 diabetes [30]. No further adaptations were considered necessary to obtain cultural fit, which is similar to experiences reported in the Swedish virtual *Body Project* study [16]. The *Body Project* is largely participant-driven given the Socratic open questions in line with dissonance-theory, which may explain why minimal changes are required to obtain efficacy in different countries. For example, in session 1 group facilitators ask what the society tells us that young women should ideally look like, by which the participants themselves define the appearance ideal in their own cultural context.

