### Procedure

A Norwegian website (www.bodyproject.no) has been designed to facilitate recruitment and project profiles are posted on Facebook and Instagram. The link will be shared via our online platforms, including Facebook, Instagram, and TikTok. Also, advertisement campaigns on social media will be run nationally. Individuals express interest by sending an e-mail to a *Body Project* mailbox hosted by Oslo University Hospital, which leads to a screening phone call to determine eligibility based on the inclusion criteria described above. In this screening call eligible participants verbally confirm to experience at least some body dissatisfaction. After providing informed consent, participants will complete baseline assessment (pretest) before being randomized into one of three arms: (i) peer-led virtual *Body Project* groups; (ii) clinician-led virtual *Body Project* groups; and (iii) educational video control group. Assessment will be repeated post intervention (posttest) and follow-up assessment after 6-months, 1-year, and 2-years. ED diagnostic interviews are conducted at baseline, 1-year, and 2-year assessments by research staff who are masked to the condition to which each participant will be randomized. Online assessment will be conducted via an online survey (Viedoc) hosted by Clinical Trials Unit (CTU), Oslo University Hospital. Randomization will be conducted by Viedoc once baseline assessment is completed. Virtually delivered *Body Project* group sessions will be implemented by use of Microsoft Teams, administered by Oslo University Hospital. Adaptations required for virtual script delivery include administration of home exercises via e-mail and using the chat function for summarizing themes during in-session group discussions rather than white boards or flip-charts used for in-person *Body Project* groups. This study is funded by the Norwegian Health Authority Region South-East (reference 2,023,032).

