### Training and supervision

Facilitators (both clinicians and peer educators) will read the intervention manual that outlines the theoretical rational of the intervention, reviews the evidence-base for the *Body Project*, and contains a detailed intervention script. Facilitators will then attend an 8-hour virtual workshop, where the conceptual rationale and supporting evidence for the *Body Project* are presented, facilitators role-play delivery of the intervention using the scripted manual, and process issues are discussed (e.g., promoting session attendance and homework completion, and recording attendance, homework completion, and verbal participation in the sessions for each group participant). All *Body Project* sessions will be videotaped, and all sessions from the first group implemented by facilitators will be rated for intervention fidelity and therapeutic competence (see below for psychometrics); supervision based on these ratings will be provided to facilitators via e-mail (feedback on what went well, and advice on how certain aspects may be improved for future sessions), which has been found to significantly increase intervention effects compared to trials that did not provide this type of ongoing supervision [10]. This study will use the same procedures for training and supervision as past *Body Project* trials [31, 33].

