#### Control condition

An educational control condition was selected to control for expectancy effects and demand characteristics. Pre-existing freely available videos allow participants to view them over the Internet to match the virtual delivery modality (1 h per week over 4 consecutive weeks). The videos contain information about how to promote a positive body image, costs associated with EDs, and how to seek help if they experience concerns related to body image, eating, body pressures, and weight. Past trials of the *Body Project* have utilized such educational videos as the control condition [15, 33, 34]. Results indicated that participants assigned to the educational control condition showed reductions in ED symptoms compared to assessment-only controls [34], but that the reductions in ED symptoms were significantly larger for *Body Project* participants than for control participants. Adherence to watching the videos will be recorded by self-report at posttest assessment. In a previous trial participants showed similar adherence to attending *Body Project* group sessions versus watching the educational videos (typically over 80%) [35].

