
### Power calculation

Sample size calculation was made for incidence of EDs assessed over a 2-year follow up via diagnostic interviews as the primary endpoint. Incidence rates were obtained from the previous Swedish virtual *Body Project* RCT [16]. Based on this trial we postulated a difference in incidence of EDs of 8.8% and 2% between groups, and a hazard ratio of 0.26 during 2 years of follow-up. Then, with a significance level of 5% and a power of 90% the estimated number of patients needed was 147 in each arm, the total number needed was 441.

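### Both Body Project arms are delivered in groups, but the models have no group or facilitator term; if outcomes correlate within groups, the continuous-outcome errors are too small, most of all for peer versus clinician

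*Protocol article*

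**What the plan says.** **Design.** Randomization is individual: "participants will complete baseline assessment (pretest) before being randomized into one of three arms" (Procedure). The Body Project "is a group-based ED prevention program based on the principles of cognitive dissonance", and within it "participants collectively critique the thin beauty ideal through a series of verbal, written, and behavioral exercises" (The intervention). Under Group facilitators, each facilitator is either a clinician or a peer, so facilitators are nested in arm. Training and supervision says that "all sessions from the first group implemented by facilitators will be rated for intervention fidelity and therapeutic competence" and that the feedback is meant for later sessions, which implies that a facilitator leads more than one group. For controls, "Pre-existing freely available videos allow participants to view them over the Internet to match the virtual delivery modality" (Control condition); no groups are described.

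**Analysis.** Statistical analyses sets the growth model at person level: "Individual variability in outcomes from posttest to 2-year follow-up was modeled adjusting for pretest outcome values". The terms are then listed: "Condition, time (coded in months since posttest), and a condition × time interaction will be added to the unconditional model". Each pair of conditions is contrasted at 1 and 2 years. The imputation uses baseline outcomes, condition and demographic factors. Onset is tested with pairwise Cox models and a proportional-hazards check. All tests use 0.05. Neither group nor facilitator appears in any of these steps.

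**Sample size.** Power calculation concludes that "the estimated number of patients needed was 147 in each arm", with no design effect. The only intraclass correlations in the article concern inter-rater agreement on fidelity and competence.

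**The concern.** This is a partially nested design: individuals are randomized, two arms are then formed into groups, and one arm is not. Women who go through four participant-driven sessions together, under the same facilitator, may end up more alike than women in different groups. The repeated-measures structure of the growth model handles correlation within a woman over time. It does not handle correlation between women in the same group.

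If such correlation exists and is left out, standard errors are too small, intervals too narrow and the false-positive rate above 5%. Peer versus clinician is the most exposed contrast, because both of its arms are grouped and facilitator type varies only between facilitators. That contrast is a stated hypothesis and the subject of a planned paper, and the article's case for wider implementation leans on it.

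**Working it through.** **Inputs from the article.** 147 per arm; alpha 0.05 (taken as two-sided); postulated 2-year incidence 8.8% and 2%; two grouped arms and one ungrouped.

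**Inputs assumed.** Group size m = 5 to 8 and outcome ICC = 0.02 to 0.10, with m = 6 and ICC = 0.05 as a central example. The article gives neither.

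**The plan's own figure.** The two-proportion formula for 8.8% versus 2%, two-sided 5% and 90% power, without a design effect, is

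n = [1.96 × √(2 × 0.054 × 0.946) + 1.2816 × √(0.088 × 0.912 + 0.02 × 0.98)]² / 0.068² ≈ 230.1, so 231 per arm.

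The stated 147 does not reproduce, and power at 147 per arm is about 73%. That is a separate matter and nothing below depends on it. It does show that 147 contains no hidden allowance for clustering.

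**Formulas for the continuous outcomes.**
- Design effect: DE = 1 + (m − 1) × ICC.
- Ratio of true to naive variance: DE for peer versus clinician (both arms grouped); (1 + DE)/2 for one Body Project arm against control (one arm grouped, equal n).
- True two-sided type I error: 2 × [1 − Φ(1.96 / √ratio)].

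| m | ICC | DE | Peer vs clinician | vs control |
|---|---|---|---|---|
| 5 | 0.02 | 1 + 4 × 0.02 = 1.08 | 5.9% | 5.5% |
| 6 | 0.05 | 1 + 5 × 0.05 = 1.25 | 8.0% | 6.5% |
| 8 | 0.10 | 1 + 7 × 0.10 = 1.70 | 13.3% | 9.2% |

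Central example in full:
- Peer versus clinician: √1.25 = 1.118; 1.96/1.118 = 1.753; two-sided tail 0.080.
- Against control: ratio (1 + 1.25)/2 = 1.125; √1.125 = 1.061; 1.96/1.061 = 1.848; two-sided tail 0.065.
- Effective size of a grouped arm: 147/1.25 ≈ 118.
- Standardized difference detectable with 80% power, peer versus clinician: (1.96 + 0.84) × √(2/147) = 0.33 under independence; 0.33 × 1.118 ≈ 0.37 with clustering.

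At the low end the effect is slight: m = 5 and ICC = 0.01 give 5.5% for peer versus clinician and 5.2% against control. A facilitator level would add to this. Suppose three groups of 6 per facilitator, with 0.02 of the 0.05 ICC at facilitator level. Then DE = 1 + 5 × 0.05 + 12 × 0.02 = 1.49 and the peer-versus-clinician error is about 10.8%.

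**Onset.** Expected events per Body Project arm are 0.02 × 147 = 2.9, so about 6 in peer versus clinician. Normal theory is poor there. As an approximation, onset was simulated as a binary outcome with beta-binomial groups and 2% incidence in both arms:
- m = 6, ICC = 0.05: a score test rejected about 6.9%; a Wald test on the log ratio about 1% (arms with no events counted as non-rejections).
- m = 8, ICC = 0.10: about 11% and 2%.

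The table's figures therefore cannot be applied to onset as they stand.

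**The case against.** **The point rests on silence.** Only the article is at hand, and a fuller analysis plan may name a group effect. The terms listed are fixed effects; the random part is not spelled out, and a reference to individual variability does not strictly rule out a group level. This carries some weight, but not enough. The article sets out the level of variability, the model-building steps, the covariate, the added terms, the contrasts and the imputation variables, and it fixes N. Followed as written, that analysis treats members of one group as independent. It does not follow that the full plan also omits the grouping; the article cannot show that.

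**The ICC may be near zero.** The contrasts are at 1 and 2 years, after four one-hour sessions, and adjust for pretest. Nothing in the article says how much group correlation lasts that long. This stands: a reader might infer that the standard errors are certainly too small, and the document does not support that. The inflation is conditional on a positive ICC, and its size is assumed.

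**The primary endpoint is incidence.** A reader might apply the 8.0% or 13.3% to the onset comparison. With about 3 events per Body Project arm the inflation depends on the test, was lower than the normal-theory figure in simulation, and was absent with a Wald test. Sparse events are the main limit there, and a clustered variance would itself be fragile. This stands too.

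**Controls watching alone is an inference.** The article says only that the videos are viewed over the Internet. It describes no control groups, so treating controls as unclustered is reasonable.

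**Conclusion.** The point holds in conditional form. The article describes two grouped arms and one ungrouped arm, while its stated models and sample size take no account of the grouping. If the outcome ICC is above zero, standard errors for the continuous outcomes are too small. For m = 5 to 8 and ICC 0.02 to 0.10, true type I error at a nominal 5% is about 5.9% to 13.3% for peer versus clinician and 5.5% to 9.2% against control. The ranking of the contrasts does not depend on the assumed values so long as the ICC is positive and similar in the two Body Project arms; the size does.

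Three stronger conclusions are not supported: that inflation is certain, that these percentages describe the onset analysis, and that the trial must recruit more. The mismatch between 147 per arm and 90% power is a different issue and lends no weight to this one.

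**What to change.** 1. Record group and facilitator identifiers for every Body Project participant. Attendance is already to be recorded for each group participant, so the burden is small.
2. In PROC MIXED, add a random intercept for group, and for facilitator where it can be estimated, in the two Body Project arms only. Treat controls as unclustered and use small-sample degrees of freedom.
3. Make the imputation consistent with the grouping. At present PROC MI would use baseline outcomes, condition and demographics, so a group effect added only at the analysis stage would not match the imputed data.
4. For onset, report a variance clustered on group, with each control as her own cluster, as a sensitivity analysis. Add a caution that few events make it unstable.
5. In Power calculation, state the assumed group size and ICC and the resulting power, without raising N.

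The cost is slightly wider intervals, a lower stated power, some model code and more care in the imputation. If the ICC proves negligible, little precision is lost.

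### The missing-data plan presents maximum likelihood and multiple imputation as one method, and lists no follow-up score among the imputation variables

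*Protocol article*

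**What the plan says.** All of this stands in the Statistical analyses section of the protocol article, except the visit schedule, which is under Procedure.

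- **Method as first named.** "We will use full information maximum likelihood (ML) estimation to impute missing data".
- **Method as the same sentence ends.** "making multiple imputation the recommended procedure for handling missing data".
- **Imputation variables.** "Missing data will be imputed using PROC MI using baseline levels of the outcomes, condition, and demographic factors (age, race, and parent education").
- **Number of imputations and pooling.** "we will impute 50 data sets", and "Model parameters and standard errors were combined following Rubin", with PROC MIANALYZE.
- **Analysis model for continuous outcomes.** A mixed effects growth model in PROC MIXED: "Individual variability in outcomes from posttest to 2-year follow-up was modeled adjusting for pretest outcome values". Pairwise condition contrasts are reported at 1 and 2 years.
- **Visits.** After the pretest, "Assessment will be repeated post intervention (posttest) and follow-up assessment after 6-months, 1-year, and 2-years".
- **Incidence.** The Cox analysis of eating disorder onset relies on censoring, and missing incidence data are not imputed.

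**The concern.** There are two linked faults.

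**Two methods are merged.** Full-information maximum likelihood estimates the model from whatever was observed and fills in nothing. Multiple imputation fills in values, analyses each completed data set and pools the results. The plan justifies the first and then specifies the second, so it does not say clearly which analysis is primary for the continuous outcomes.

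**The listed imputation variables do not match the analysis model.** The growth model relates each participant's posttest, 6-month, 1-year and 2-year scores to one another. The list contains only baseline outcomes, condition and demographics. Consider a participant who is seen at posttest and 6 months and then leaves. Her observed scores stay in the growth model, but on the plain reading they do not inform the values drawn for her later visits. PROC MIXED fitted to the observed visits would have used them directly.

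At stake are the 1- and 2-year contrasts on risk factors, symptoms and the other continuous outcomes. Information is lost, and a bias can arise if early response drives dropout differently between arms. A live virtual group and self-watched videos could plausibly lose responders and non-responders at different rates.

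**Working it through.** The plan gives no figure to reproduce here: it states no expected dropout, no correlation between visits and no dropout mechanism. The check has three steps.

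**1. Reading the text.** Five visits are planned and four of them are post-baseline. The imputation list names none of those four, yet the analysis model is fitted to exactly those four, with the pretest as covariate.

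**2. What imputation from baseline does to within-person correlation.** Assume that the pretest correlates 0.5 with each follow-up score. A 2-year value drawn from pretest, condition and demographics is then linked to the same person's posttest score only through the pretest:

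0.5 × 0.5 = 0.25, against an assumed 0.6 to 0.75 in observed pairs.

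The growth model estimates its covariance from a mixture of the two. This is the uncongeniality.

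**3. Effect on the 2-year contrast (simulation).**

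- From the Power calculation section: 147 per arm. Two arms are compared.
- Assumed: normal scores with SD 1; pretest-to-follow-up correlation 0.5; correlation between follow-ups 0.6 or 0.75; 2-year score missing with probability 10%, 20% or 30% at the mean posttest score; where dropout depends on the posttest score, the log-odds change by 1 per SD.
- Analysis: ANCOVA at 2 years, 20 imputations, Rubin's rules, 500 runs per setting.
- Simulation error: with a sampling SD of about 0.12, it is about 0.12/√500 = 0.005 SD.

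Absolute bias of the 2-year contrast, in SD, when imputing from baseline and condition only:

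| Missing at mean posttest | Correlation between follow-ups | Dropout related to posttest in one arm only | Related in opposite directions |
|---|---|---|---|
| 20% | 0.60 | 0.068 | 0.147 |
| 20% | 0.75 | 0.101 | 0.207 |
| 30% | 0.60 | 0.095 | 0.203 |
| 30% | 0.75 | 0.139 | 0.290 |

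With 10% missing included, the ranges are 0.04 to 0.14 (one arm) and 0.09 to 0.29 (opposite). The sign depends on which arm loses which participants. If dropout is unrelated to the posttest score, or equally related in both arms, there is no bias beyond simulation error. With the posttest and 6-month scores added to the imputation model, bias is at most 0.01 SD in every setting.

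Precision, as the ratio of mean standard errors (baseline-only over all visits):

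- 20% missing, correlation 0.60, one-arm mechanism: 0.115/0.112 = 1.03.
- 30% missing, correlation 0.75, dropout unrelated to posttest: 0.123/0.112 = 1.10.

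Most settings lie between 2% and 10%.

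**Check with a growth model.** ANCOVA at one visit is not the planned estimator. A linear growth model was therefore also run (147 per arm, 25 to 27% missing at 2 years, true effect −0.25 SD, 300 runs, 5 imputations):

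| Dropout mechanism | Baseline-only imputation | Likelihood on observed visits |
|---|---|---|
| One arm | −0.29 | −0.24 |
| Opposite | −0.36 | −0.24 |
| Same in both arms | −0.25 | −0.25 |

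Under the same mechanism in both arms, imputation had a sampling SD about 8% larger. The pattern matches the ANCOVA results. The size of any bias at 1 year was not calculated.

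**The case against.** **The list may not be exhaustive.** The plan does not say that these are the sole variables or that each visit is imputed separately. PROC MI run jointly in wide format would let the follow-up visits inform one another, with the listed items as additional predictors. This stands: the text does not prove that follow-up scores will be left out. But it does not describe the joint run either, and the list followed as written leaves them out.

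**The detail belongs in the analysis plan.** A journal article need not specify an imputation model in full, and an analysis plan may exist. That would answer silence. Here the article names the software, the variables, the number of imputations and the pooling, and attributes imputation to a method that does not impute.

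**The operational intent is clear.** The steps after the faulty sentence all describe multiple imputation, so that is probably what is meant. This limits the first fault to wording. It does not settle the second.

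**Likelihood is not simply the weaker assumption.** The imputation list includes demographics and the baseline levels of several outcomes, whereas the growth model is stated to adjust for pretest values. Neither set contains the other. This stands, and either method is acceptable once properly specified.

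**Stronger readings that the document does not support.** A reader might infer that observed posttest and 6-month scores are thrown away. They are not: they remain in the growth model and are absent only as predictors of missing values. A reader might also infer that the contrasts are biased whenever dropout depends on early response. The calculations show little or no bias when that dependence is the same in all arms. Nor is the trial's main result at risk: the sample size rests on eating disorder incidence, which is not imputed.

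**Conclusion.** The point holds in a limited form. The statement that maximum likelihood imputes is wrong as written. The listed imputation variables, taken at face value, omit every post-baseline score and are uncongenial with the growth model.

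Under the assumed inputs, the cost is a somewhat larger standard error in most settings. Material bias at 2 years requires dropout to depend on the posttest score differently by arm, and every magnitude rests on correlations, missing rates and mechanisms that the document does not give. If the intended PROC MI run is joint across visits, the second fault disappears and only the wording needs correction. The scope is the continuous outcomes; the incidence endpoint and the sample size are untouched.

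**What to change.** Name one method for the continuous outcomes and delete the statement that maximum likelihood imputes. Either option will do:

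1. **Likelihood without imputation.** Fit PROC MIXED to all observed visits and drop the PROC MI and PROC MIANALYZE steps. Baseline and demographic predictors of dropout may be added as covariates if wanted.
2. **Multiple imputation.** Keep PROC MI, but impute in wide format with the outcome at every visit in the imputation model, together with condition and the baseline variables already listed. Then fit the growth model and pool as planned.

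A delta-adjusted sensitivity analysis at 2 years would be a useful addition but is optional; its absence is not part of the error.

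The cost is a few sentences in the protocol or analysis plan. Option 1 needs less programming than planned; option 2 needs a change to the imputation call. No visit, measure or sample size changes. The choice should be fixed before outcome data are seen by arm, because the present wording could be read to permit either method afterwards.

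### With about 3 onsets expected per Body Project arm, the planned Cox hazard ratio has no finite estimate in about 5% of trials for a given arm (10% for either), and a Wald test would cost about 10 points of power

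*Protocol article*

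**What the plan says.** The Power calculation section of the protocol article sizes the trial on eating-disorder incidence over 2 years, which it names as the primary endpoint: "we postulated a difference in incidence of EDs of 8.8% and 2% between groups, and a hazard ratio of 0.26". The result is that "the estimated number of patients needed was 147 in each arm, the total number needed was 441", "with a significance level of 5% and a power of 90" per cent.

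The Statistical analyses section fixes the method for this endpoint: "Cox proportional hazard models, fit with STATA [55] will test whether eating disorder onset over 2-year follow-up was significantly lower in each condition versus each" of the others. For reporting, "Hazard ratios and number needed to treat (NNT; [56]) are provided as measures of effect size". The section does not say whether the p-value comes from the Wald, score or likelihood-ratio test. Missing incidence data are censored and not imputed.

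**The concern.** An ordinary Cox model needs at least one onset in each of the two arms compared to give a finite hazard ratio. With no onsets in an arm, the log hazard ratio runs to minus infinity (or plus infinity, if that arm is the reference). The Wald interval is then meaningless and the Wald p-value is close to 1. This happens when an active arm has done as well as it possibly can. With only a few onsets in an arm, the estimate is finite but the Wald test loses power against the score test on the same data.

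At stake are the effect size for the endpoint on which the trial is sized and, if the Wald statistic is used, the significance decision. Leaving the statistic open also leaves room to choose it after the data are seen. The peer-versus-clinician contrast shares the estimability problem, because both of its arms expect about 3 onsets if both are at 2%.

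**Working it through.** **Inputs.** From the Power calculation section: 147 per arm, incidence 8.8% (control) and 2% (active), hazard ratio 0.26, alpha 5%, power 90%. From the Design section: two active arms and one control. Two-sided testing and complete follow-up are my assumptions unless stated.

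**1. The plan's own figure.** The 147 per arm at 90% power is not reproduced.
- Two proportions, pooled variance: 231 per arm.
- Schoenfeld with hazard ratio 0.26: 24 events, and 24 / (0.088 + 0.02) = 222 per arm.
- The two rates themselves imply a hazard ratio of ln(0.98) / ln(0.912) = 0.219. Schoenfeld with that value needs 19 events, or 176 per arm.

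At 147 per arm, power is 73% (two proportions) or 77% (Schoenfeld, hazard ratio 0.26, 15.9 events). This shortfall is a sample-size matter and exists before any choice of Cox test.

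**2. Expected onsets.** Control: 147 × 0.088 = 12.9. Each active arm: 147 × 0.02 = 2.94.

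**3. Chance of an arm with no onsets.**

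| Assumption | One given active arm | At least one of two |
|---|---|---|
| 2% incidence, n = 147 | 0.98^147 = 5.1% | 1 − (1 − 0.051)² = 10.0% |
| Hazard ratio 0.26: incidence 1 − 0.912^0.26 = 2.37%, 3.5 onsets | 3.0% | 5.8% |
| 2% incidence, assumed 20% loss (147 × 0.8 = 117.6) | 9.3% | 17.7% |

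None of these depends on which test supplies the p-value.

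**4. Wald power in closed form.** SE of the log hazard ratio ≈ √(1/12.936 + 1/2.94) = 0.646. |ln 0.219| = 1.518, and 1.518 / 0.646 = 2.349. Power = Φ(2.349 − 1.960) = 65%.

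**5. Simulation of one active arm against control.** 200,000 trials, onset found at 12 or 24 months, Breslow ties, zero-onset trials counted as non-significant by Wald:

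| Test | Power, 8.8% vs 2% | Rejection rate, 2% vs 2% |
|---|---|---|
| Wald | 65.2% | 0.3% |
| Score (log-rank) | 76.7% | 4.5% |
| Likelihood ratio | 78.0% | 7.5% |
| Firth penalised likelihood ratio | 74.6% | 2.8% |

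Smaller runs, with grouped or continuous onset times, gave 65–67% for Wald, 75–77% for score and 78–79% for likelihood ratio. In one run of 60,000 trials, 10.7% were significant by the score test but not by Wald. With a hazard ratio of 0.26 in place of the 2% rate, Wald power is 60–62% and score or log-rank power 69–71%.

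**6. An example.** Take 13 onsets against 0, with 147 per arm. The Wald p-value is near 1. The two-proportion score statistic is z = 3.7 and Fisher's exact p = 0.0002. The risk difference is 13/147 = 8.8 percentage points, so the NNT is 147/13 = 11.3 although the hazard ratio has no finite value.

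**7. Splitting the gap from 90%.** From 90% to about 76% is the sample size (14 points). From about 76% to about 65% is the Wald test, if used (11 points; 9 to 12 across the runs at the plan's two incidence rates).

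**The case against.** The strongest reply is that the article never names the Wald test, and that the choice of statistic and the handling of sparse events usually belong in a statistical analysis plan, which is not shown. The score and likelihood-ratio tests come from the same Cox model and remain defined with no onsets in one arm; in the 13-versus-0 example the score test is decisive. The NNT, also planned, can still be calculated. All of this stands, and it makes the 65% conditional.

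It does not remove the estimability problem. The article commits to an ordinary Cox hazard ratio at an incidence where that quantity foreseeably does not exist, whichever test is used and whatever detail is added about p-values.

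A reader might go further and infer that the Cox analysis breaks down. The figures do not support that: a given active-versus-control hazard ratio is estimable in about 95% of trials, and both are in about 90%. A reader might also infer that the Cox test takes power from 90% to 65%. Most of that fall is due to the sample size. Finally, a reader might infer a power loss for peer versus clinician. The article postulates no difference there, so none can be calculated. The 0.3% Wald rejection rate at 2% versus 2% shows only that the test is very conservative at that null.

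**Conclusion.** The concern holds in limited form and should be acted on. On the plan's own inputs, the hazard ratio named as an effect size for onset has no finite estimate in about 5% of trials for a given active arm and about 10% for at least one of the two. With the stated hazard ratio of 0.26 the figures are about 3% and 6%. Losses to follow-up would raise them.

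If the Wald test of the coefficient is used, which the article neither states nor excludes, it costs about 10 points of power for one active-versus-control contrast: about 65% against about 76% for the score test. This rests on two-sided 5% testing, full follow-up and the postulated 8.8% and 2%. It is additional to the sample-size shortfall, and smaller than it.

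**What to change.** In the analysis plan, before unblinding:
- Take the p-value for each pairwise onset contrast from the log-rank (score) test, and name that test as decisive.
- Report the hazard ratio from a Firth-penalised Cox model with a profile-likelihood interval, at least when an arm has few or no onsets. It stays finite when one arm has none.
- Base the NNT on the 2-year risk difference, with an interval suited to small counts.

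The cost is a few sentences and a few lines of code, with no extra participants. There are two downsides. The penalised hazard ratio is shrunk slightly towards 1. Its interval can occasionally disagree with the log-rank p-value (power 74.6% against 76.7%, null rejection 2.8% against 4.5%), which is why one test must be named as decisive. The change does not restore 90% power; that needs the sample size to be revisited separately.
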